### Statistical analysis

#### Sample size

The sample size is based on an individually randomised controlled trial without accounting for stratification by clinic. Clinical significance was considered to be a difference of at least 0.5% (7 mmol/mol) in mean HbA1c between the groups and is based on current guidelines which recommend intensification of therapy when HbA1c levels remain 0.5% (7 mmol/mol) above target [19]. The sample size was calculated using HbA1c in %. Using a significance level of 0.05, power of 0.8, clinically significant difference of 0.5%, and standard deviation of 1.3% for HbA1c [24], the required number of participants in each group is 108, a total of 216. This is equivalent to a difference in the mean HbA1c of 7 mmol/mol between the groups with a standard deviation of 14 mmol/mol [24]. Assuming a 20% attrition rate, the required sample size inflates to 270 (135 in each group). Allowing for 10% clinic attrition and assuming six participants per clinic, we require 50 clinics with six participants per clinic (150 in each group).

Figure 1 shows the minimum number of clinics and participants per clinic required for 20% participant attrition and 10% clinic attrition. The figure shows that it is possible to recruit 300 participants in a variety of ways; for example, 25 clinics with 12 participants per clinic, 30 clinics with 10 participants per clinic, 50 clinics with six participants per clinic, and 75 clinics with four participants per clinic. Four participants per clinic was the minimum recommended to allow for estimation of the correlation in outcome measure between participants in the same group and clinic. From prior knowledge of recruitment patterns from the Stepping Up Study [24] it was decided to recruit 50 clinics with six participants per clinic.

**Fig. 1 Fig1:**
[figure not shown]
Total sample size versus number of clinics

#### Data collection and preparation

An in-house, web-based, purpose-built recruitment database will be used to document all practices approached to participate in the study. Once consented to the study, REDCap© will be used to store all clinic, GP, and practice nurse (PN) characteristics. All clinic, staff, and participant data will be collected at baseline and 12 months and entered into the database by research assistants using either a desktop computer or tablet. Data from CAVs and any technical issues or adverse events associated with the r-CGM device will be logged by research assistants in REDCap©.

HbA1c data will be collected 6-monthly from the same pathology laboratory for each patient and collated in a Microsoft Excel 2016 file. Participants will be encouraged to have their HbA1c levels collected at 3 and 9 months, but this will not be compulsory. The pathology data will be merged with the clinical patient data in STATA version 15.1 [25].

An in-house, web-based, purpose-built participant tracking database will be used to track changes in patient medication and the progress of patients throughout the study.

#### Trial profile

A study flow diagram (Fig. 2) will be used to summarise the progress of participants throughout the trial, from eligibility assessment to analysis of the primary outcome at 12 months [26].

**Fig. 2 Fig2:**
[figure not shown]
Study flow diagram to be completed for trial. HbA1c glycated haemoglobin

#### Descriptive statistics

STATA version 15.1 (StataCorp, College Station, Texas) will be used for all analyses. Practice, GP, PN, and participant characteristics at baseline will be summarised (Tables 1 and 2). Continuous measures will be summarised using means and standard deviations or medians and interquartile ranges for skewed distributions. Categorical variables will be summarised using frequencies and percentages. Where applicable, the number of missing values will be specified and percentages for categorical variables will be based on the available data only.

**Table 1 Tab1:** Baseline characteristics of practices, general practitioners (GPs), and practice nurses (PNs)

Characteristic	Measure	*n* (%)	Missing *n* (%)
Practices			
Practice billing			
Bulk billing	*n* (%)		
Private billing	*n* (%)		
Community health centre	*n* (%)		
Practice location			
Major city	*n* (%)		
Inner regional	*n* (%)		
Outer regional	*n* (%)		
Number of GPs per practice	Median (IQR)		
Number of PNs per practice	Median (IQR)		
GPs			
Age group (years)			
25–34	*n* (%)		
35–44	*n* (%)		
45–54	*n* (%)		
55–64	*n* (%)		
65 or over	*n* (%)		
Female	*n* (%)		
Working hours per week	Mean (SD)		
Years of experience	Mean (SD)		
PNs			
Age group (years)			
25–34	*n* (%)		
35–44	*n* (%)		
45–54	*n* (%)		
55–64	*n* (%)		
65 or over	*n* (%)		
Female	*n* (%)		
Working hours per week	Mean (SD)		
Years of experience	Mean (SD)		

*IQR* interquartile range, *SD* standard deviation

**Table 2 Tab2:** Baseline characteristics of participants by study group

Participant characteristics		Intervention (*n*=)	Missing *n* (%)	Control (*n*=)	Missing *n* (%)
Age (years)	Mean (SD)				
Female	*n* (%)				
Country of birth					
Australia	*n* (%)				
Other	*n* (%)				
Highest level of education					
Primary or never attended	*n* (%)				
Secondary or trade/TAFE	*n* (%)				
University diploma/degree	*n* (%)				
Employed	*n* (%)				
IRSD (decile)	Median (IQR)				
Healthcare card holder	*n* (%)				
Diabetes duration (years)	Median (IQR)				
History of severe hypoglycaemia^a^	*n* (%)				
HbA1c					
mmol/mol	Median (IQR)				
%	Median (IQR)				
Individualised target over 7%	*n* (%)				
Diabetes distress (PAID)	Mean (SD)				
Severe diabetes distress (PAID ≥ 40)	*n* (%)				
Weight (kg)	Mean (SD)				
Blood pressure (mmHg)					
Systolic	Mean (SD)				
Diastolic	Mean (SD)				
Current medications					
Non-insulin hypoglycaemic agents					
Metformin	*n* (%)				
Sulphonylureas	*n* (%)				
DPP4i	*n* (%)				
GLP1	*n* (%)				
Other	*n* (%)				
Insulin	*n* (%)				
Number of hypoglycaemic agents					
1–2 agents	*n* (%)				
3 agents	*n* (%)				
4–5 agents	*n* (%)				

*GP* general practitioner, *HbA1c* glycated haemoglobin, *IQR* interquartile range, *IRSD* index of relative socio-economic disadvantage (calculated using patient postcode [33]), *PAID* problem area in diabetes, *PN* practice nurse, *SD* standard deviation, *TAFE* technical and further education

^a^ Hypoglycaemia requiring third party assistance

*Medicare is managed by the Department of Human Services and is Australia’s publicly funded healthcare system funding primary health care for Australian citizens and permanent residents

*The PBS is managed by the Department of Human Services and is a list of medicines available to be dispensed to patients at a government-subsidised price. The scheme is available for all Australian residents

*Public hospitals are funded by the state, territory and Australian governments, and managed by state and territory governments. Victorian Admitted Episodes Dataset (VAED) and the Victorian Emergency Minimum Dataset (VEMD) provide hospital costings for Victorian patients

#### Statistical modelling

##### Primary and secondary outcomes

Whilst our primary outcome is HbA1c at 12 months post-intervention, we will estimate the between-group difference in mean HbA1c at 6 and 12 months with the same linear mixed-effects model using restricted maximum likelihood estimation. As the data are longitudinal, HbA1c measured at baseline, 6 months, and 12 months will be included in the model as the dependent variable and study groups (intervention and control) and time of the pathology result (baseline, 6, and 12 months) will be collected as fixed effects. A two-way interaction term between study group and time will be included in the model to estimate the between-group difference in mean HbA1c at 6 and 12 months, but we will constrain the estimated baseline means to be equal. The model will include random intercepts for clinic (as individuals will be clustered within clinics) and individuals (as patient measures are repeated within individuals). An unstructured variance-covariance structure will be assumed for the random effects variables as correlations between measurements within individuals and correlations between measurements in participants from the same clinic are expected to be unique.

Age, index of relative socio-economic disadvantage (IRSD), and a history of severe hypoglycaemia are known to be at least moderately associated with HbA1c [9, 27]. In a secondary analysis, the outcome measure will be adjusted for these potential confounders. These measures will be included as fixed effects in the model.

An intention-to-treat (ITT) approach will be used where participants will be analysed according to the study group they were assigned, and all participants will be included in the analysis, consistent with mixed model analysis [28]. The estimated mean HbA1c levels at baseline, 6 months, and 12 months will be plotted for each study group with 95% confidence intervals.

The same statistical modelling approach described for HbA1c will be used for the secondary outcomes, percentage time in target and diabetes-specific distress at 12 months. Transformations for skewed outcome measures will be considered.

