### Inclusion criteria

Eligible participants will be aged 18–80 years, active patients of the practice (defined as three or more visits to the practice in the last 2 years), have had T2D for at least 1 year with their most recent HbA1c (in the previous 1 month) ≥ 7 mmol/mol (0.5%) above their individualised target (see below) while on at least two non-insulin hypoglycaemic therapy and/or insulin (therapy stable for the last 4 months). Our general glycaemic target is set at 53 mmol/mol (7%) while patients with a history of severe hypoglycaemia (requiring assistance from a third person) or who report impaired awareness of hypoglycaemia (i.e. are unable or have reduced capacity to recognise the early signs and symptoms of hypoglycaemia, which may impede timely self-treatment) will have a target of 64 mmol/mol (8%). In the setting of this pragmatic trial we will allow GPs to indicate a personalised target for a participant if they feel that it should differ from the two pre-specified targets set out above.

Patient exclusion criteria will include: any debilitating medical condition (e.g. unstable cardiovascular disease (CVD), severe mental illness, end-stage cancer), an estimated glomerular filtration rate (eGFR) < 30 ml/min/1.73m^2^, proliferative retinopathy, pregnancy, lactating or planning pregnancy, unable to speak English/give informed consent, unwilling to use r-CGM or follow study protocol, allergy to adhesive tape, diagnosis of T2D within the past 12 months, and any condition that makes monitoring diabetes using HbA1c unreliable (e.g. haemoglobinopathy, iron deficiency anaemia).

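### In the primary model, 'unstructured' is attached to single random intercepts, where it does nothing; read with default residuals the model is compound symmetry, and the 12-month standard error can be wrong in either direction

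*SAP article*

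**What the plan says.** The section on primary and secondary outcomes in the SAP article sets out a linear mixed model fitted by restricted maximum likelihood. HbA1c at baseline, 6 and 12 months is the outcome. The fixed effects are group, time and their interaction, with the two baseline means constrained to be equal. On the random part it says: "The model will include random intercepts for clinic (as individuals will be clustered within clinics) and individuals". It then adds: "An unstructured variance-covariance structure will be assumed for the random effects variables". The reason given is that the correlations within a person, and between people at the same clinic, are expected to be unique.

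The section names no residual covariance structure, random slope, visit-level random effect or robust standard error. The only planned sensitivity analysis of this model, a pattern-mixture analysis, varies the missing-data assumption and leaves the covariance alone. The same modelling approach is carried over to time in target and PAID, which Table 4 shows at baseline and 12 months.

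**The concern.** The sentence asks for flexibility but places it where it has no effect. A covariance structure among random effects matters only when one level has two or more of them. Here each level has one, so an analyst who follows the text and accepts default residuals fits compound symmetry.

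This bears on the primary result because baseline is part of the outcome vector and its means are constrained equal. The 12-month difference is therefore adjusted for the chance baseline difference through the modelled baseline-to-12-month covariance, and its standard error uses the modelled variance. Under compound symmetry both quantities are averages over visits and need not suit the 12-month comparison. Nothing else in the plan would reveal or correct a mismatch.

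**Working it through.** **1. The plan's own sample size.** The inputs are "clinically significant difference of 0.5%, and standard deviation of 1.3% for HbA1c", 5% significance (two-sided assumed; the document does not say) and 80% power. The normal approximation gives 2 × (1.960 + 0.842)² × 1.3² / 0.5² = 106.1, so 107 per group. The t-test version gives 107.09, so 108, as the plan states. Then 216 / 0.8 = 270 and 270 / 0.9 = 300. The sample size reproduces and is not affected by this point, since it rests on a plain comparison of two means.

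**2. What the model implies.** Let the clinic, person and residual variances be c, p and e, with independent residuals of equal variance.
- Variance at every visit: c + p + e.
- Covariance of every pair of visits in one person: c + p.
- Correlation of every pair: (c + p) / (c + p + e).

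So there is one variance and one correlation, whatever structure is declared for the intercepts.

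**3. Effect on the 12-month contrast.** With n per arm and complete data, the constrained-baseline estimate is d12 − ρ·d0. Here d12 and d0 are the observed group differences at 12 months and baseline. Compound symmetry uses σ² = the mean of the three visit variances and ρ = the mean of the three covariances divided by σ².
- Model variance: (2/n) × σ²(1 − ρ²).
- True variance of the same estimate: (2/n) × (σ12² − 2ρσ0,12 + ρ²σ0²).
- Type I error: 2 × [1 − Φ(1.96 × model SE / true SE)].

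The clinic intercept is left out. It adds the same constant to every variance and covariance, so it cannot free the pattern over visits.

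**4. Assumed covariance patterns, 108 per arm, complete data.** The document gives a single SD, 1.3%, and no correlations. All visit-specific values below are assumptions. Correlations are in the order 0–6, 0–12, 6–12 months.

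| | SDs at 0, 6, 12 months | Correlations | Model SE | True SE | Type I error |
|---|---|---|---|---|---|
| a | 1.3, 1.3, 1.3 | 0.60, 0.60, 0.60 | 0.1415 | 0.1415 | 5.0% |
| b | 1.3, 1.3, 1.3 | 0.65, 0.45, 0.65 | 0.1437 | 0.1597 | 7.8% |
| c | 1.0, 1.2, 1.3 | 0.60, 0.60, 0.60 | 0.1289 | 0.1439 | 7.9% |
| d | 1.0, 1.2, 1.3 | 0.65, 0.45, 0.65 | 0.1305 | 0.1580 | 10.5% |
| e | 1.1, 1.3, 1.5 | 0.60, 0.40, 0.60 | 0.1521 | 0.1871 | 11.1% |
| f | 1.3, 1.2, 1.1 | 0.65, 0.45, 0.65 | 0.1334 | 0.1382 | 5.9% |
| g | 1.5, 1.3, 1.1 | 0.60, 0.60, 0.60 | 0.1445 | 0.1234 | 2.2% |

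Pattern b in full:
- ρ = (0.65 + 0.45 + 0.65) / 3 = 0.583.
- Model variance = (2/108) × 1.69 × (1 − 0.340) = 0.0206, SE 0.1437.
- True variance = (2/108) × 1.69 × (1 − 2 × 0.583 × 0.45 + 0.340) = 0.0255, SE 0.1597.
- SE ratio = 0.900, so type I error = 2 × [1 − Φ(1.76)] = 7.8%.

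Pattern g in full:
- σ² = (2.25 + 1.69 + 1.21) / 3 = 1.717.
- ρ = [(1.170 + 0.990 + 0.858) / 3] / 1.717 = 0.586.
- Model variance = (2/108) × 1.717 × (1 − 0.343) = 0.0209, SE 0.1445.
- True variance = (2/108) × (1.21 − 2 × 0.586 × 0.990 + 0.343 × 2.25) = 0.0152, SE 0.1234.
- SE ratio = 1.17, so type I error = 2.2%.

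**5. With attrition.** With 135 per arm, 10% lost before 6 months and 20% by 12 months, unrelated to HbA1c, the errors barely move: b 7.8%, c 8.1%, d 10.7%, e 11.4%, g 2.1%. These figures concern the standard error only and say nothing about bias from informative dropout.

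**6. What a free visit covariance costs.** In pattern a, where compound symmetry is true, the large-sample SE under an unstructured visit covariance is also 0.1415. In pattern b it is 0.1580 and in pattern g 0.1198. Each is slightly below the true SE of the compound-symmetry estimate, so freeing the covariance loses no precision in these cases.

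**The case against.** Four points can be made for the plan.

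First, the residual structure is not stated. The reason given for the structure may signal that a free within-person covariance was intended and loosely worded in a condensed article. That is fair: compound symmetry follows from default residuals, and the plan does not announce it. But the text assigns the structure to the random effects, and a literal reading leads to the restricted model. If the reason meant only that the clinic and person correlations differ from each other, two separate intercepts already provide that, and the word is still idle.

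Second, a person-level random intercept is a common choice for three visits. With complete data and randomisation the estimate d12 − ρ·d0 is unbiased for any ρ. This stands: with complete data only the model-based SE, interval and p value are at issue.

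Third, a reader might infer that the interval must be too narrow. The document does not support that. It gives no SD by visit and no correlation, and patterns with falling variance go the other way: SDs of 1.4, 1.25 and 1.1 with correlations 0.55, 0.40 and 0.70 give 4.9%, and pattern g gives 2.2%.

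Fourth, a reader might infer that the entry rule, HbA1c "≥ 7 mmol/mol (0.5%) above their individualised target", truncates the modelled baseline and so makes equal variances untenable. The rule applies to the most recent HbA1c in the previous month, and the document does not say that this value is the baseline analysed. The floor also differs between participants, because targets are 7%, 8% or set by the GP. Treat-to-target care could narrow the 12-month spread as well. A narrower baseline is possible but not established.

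**Conclusion.** The concern holds in a limited form. As written, the covariance statement has no effect, and with default residuals the primary model imposes equal variances and one common within-person correlation, against the plan's stated expectation. If the true covariance departs from this, the inference on the primary outcome is wrong by an amount and in a direction that the document cannot settle. Under the assumed patterns the model SE runs from about 19% too small (0.1521 / 0.1871 = 0.81) to about 17% too large (0.1445 / 0.1234 = 1.17). Type I error runs from about 2% to about 11%. If compound symmetry holds, there is no error.

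Under dropout there is a further dependence. The Discussion relies on the mixed model being valid when data are missing at random, and likelihood inference under that assumption also needs the covariance to be right. No size can be put on this from the document.

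For time in target and PAID, with two visits, there is only one correlation, so only the equal-variance restriction is at issue.

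This should be corrected before analysis. It does not show that the planned analysis is invalid.

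**What to change.** Keep the clinic random intercept. Replace the individual random intercept with an unstructured 3×3 residual covariance across baseline, 6 and 12 months within individual, and say so in place of the present sentence. In the named software the random part would be `|| clinic: || id:, nocons residuals(unstructured, t(time))`. Use the 2×2 version for time in target and PAID.

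State a fallback for non-convergence, for example the random-intercept model with robust standard errors clustered by clinic. Check beforehand that the software offers this with restricted maximum likelihood; if it does not, name the estimation method that the fallback will use.

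The cost is one sentence and one line of code. The within-person part goes from two covariance parameters (person and residual variance) to six (three variances and three covariances), with about 300 participants planned. The sample size does not change.

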### Primary outcome

The primary outcome measure is the difference in mean HbA1c at 12 months between the intervention and control groups.

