#### Explanatory analysis

We will conduct two planned subgroup analyses for HbA1c at 6 and 12 months. In the first analysis, a two-way interaction term between history of severe hypoglycaemia (yes/no) and study group will be included in the primary analysis model to examine if there is a different intervention effect between those with a history of severe hypoglycaemia compared to those without. For the second subgroup analysis, a two-way interaction term between study group and type of HbA1c target (personalised vs general) will be added to the primary analysis model, to examine whether the intervention effect varies according to whether participants have a personalised HbA1c target that is different from the general target of 7% or not.

Results from the primary, secondary, and sub-analyses will be presented as shown in Tables 3, 4, 5, and 6. Estimates of the between-group difference for mean outcomes will be reported with their respective 95% confidence intervals and *p* values.

**Table 3 Tab3:** Estimated HbA1c and between-group differences for intervention and control groups

	Estimated mean HbA1c (95% CI)		Difference in estimated mean HbA1c and general HbA1c target of 7%		Unadjusted		Adjusted*	
	Intervention group (*n*=)	Control group (*n*=)	Intervention group (*n*=)	Control group (*n*=)	Intervention vs. Control between-group differences (95% CI)	*P* Value	Intervention vs. Control between-group differences (95% CI)	*P* Value
Baseline								
6 months								
12 months								

*Adjusted for age, IRSD and history of severe hypoglycaemia

**Table 4 Tab4:** Estimated percentage time in target, diabetes distress and between-group differences for intervention and control groups (secondary analyses)

	Estimated mean % time in target (95% CI)		Unadjusted		Adjusted*	
	Intervention group (*n*=)	Control group (*n*=)	Intervention vs. Control between-group differences (95% CI)	*P* Value	Intervention vs. Control between-group differences (95% CI)	*P* Value
Percentage time in target (%)						
Baseline						
12 months						
	Estimated mean diabetes distress (95% CI)		Unadjusted		Adjusted*	
	Intervention group (*n*=)	Control group (*n*=)	Intervention vs. Control between-group differences (95% CI)	*P* Value	Intervention vs. Control between-group differences (95% CI)	*P* Value
Diabetes-specific distress (PAID)						
Baseline						
12 months						

*Adjusted by age and IRSD

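### The primary 12-month HbA1c model leaves out three pre-specified baseline covariates that the plan itself calls predictive: a valid analysis, with a modest and avoidable loss of precision

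*SAP article*

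**What the plan says.** The endpoint is defined under Primary outcome: "The primary outcome measure is the difference in mean HbA1c at 12 months between the intervention and control groups".

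Under Primary and secondary outcomes, the SAP article specifies a linear mixed model for HbA1c at baseline, 6 and 12 months. It has group, time and their interaction, baseline means constrained to be equal, and random intercepts for clinic and participant.

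The same section then says that age, IRSD and history of severe hypoglycaemia "are known to be at least moderately associated with HbA1c", and continues: "In a secondary analysis, the outcome measure will be adjusted for these potential confounders". They are to enter as fixed effects.

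Table 3 (Explanatory analysis) gives unadjusted and adjusted differences side by side, each with a confidence interval and a p value. The footnote to the second reads "Adjusted for age, IRSD and history of severe hypoglycaemia". The model without the three covariates is therefore the primary one. The article gives no reason for that order and no correlation or R² for any of the covariates.

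**The concern.** Randomisation is within clinic, so any imbalance in these variables between the groups is due to chance and the confounder label does not fit. Adjusting for a predictive baseline variable in a randomised trial removes explained variance from the treatment contrast. The plan has already chosen the covariates, asserted that they predict the outcome and written the adjusted model, yet it takes its deciding p value from the model that is expected to be the less precise.

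Because the model is linear, the adjusted and unadjusted 12-month differences estimate the same quantity, so changing the order would not change the question. The Discussion defends random clinic effects on grounds of power and efficiency. By that same criterion, leaving out declared predictors calls for a reason. At stake is some width of the primary interval, and the possibility that Table 3 shows two p values of which the expected sharper one cannot count as the trial's answer.

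**Working it through.** **1. The plan's own figure.** Inputs (Sample size): "Using a significance level of 0.05, power of 0.8, clinically significant difference of 0.5%, and standard deviation of 1.3% for HbA1c". Stated result: "the required number of participants in each group is 108, a total of 216".

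n per group = 2 × (1.960 + 0.842)² × 1.3² / 0.5² = 2 × 7.85 × 1.69 / 0.25 ≈ 106.1. That is 107 by the normal approximation and 108 by the two-sample t calculation (two-sided), so the figure reproduces. Attrition also reproduces: 216/0.8 = 270 and 270/0.9 = 300.

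The calculation uses the marginal SD of 1.3%. It takes no credit for baseline HbA1c or for the three covariates, so the planned 80% power does not depend on adjusting for them.

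**2. The planned primary model.** A plain comparison of 108 per group has SE = 1.3 × √(2/108) = 0.177 and a 95% half-width of 0.347. Let ρ be the correlation of HbA1c between visits (assumed, and equal for all pairs, as a participant random intercept implies). With complete data and equal baseline means, the SE of the 12-month difference is 0.177 × √(1 − ρ²).

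| ρ | SE | Half-width |
|---|---|---|
| 0.3 | 0.169 | 0.331 |
| 0.5 | 0.153 | 0.300 |
| 0.7 | 0.126 | 0.248 |

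**3. Adding the three covariates.** Let R² be the share of HbA1c variance they jointly explain (assumed, the same at each visit). The residual correlation is ρc = (ρ − R²)/(1 − R²), and the SE is 0.177 × √[(1 − R²)(1 − ρc²)].

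Example with ρ = 0.5 and R² = 0.10: ρc = 0.40/0.90 = 0.444; (0.90)(1 − 0.1975) = 0.722; SE = 0.177 × 0.850 = 0.150. The fall is 1 − 0.850/0.866 = 1.9%.

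| R² | Fall in SE, ρ = 0.3 | ρ = 0.5 | ρ = 0.7 | Power for 0.5% at ρ = 0.5 |
|---|---|---|---|---|
| 0 | – | – | – | 90.4% |
| 0.02 | 0.6% | 0.3% | 0.2% | 90.6% |
| 0.05 | 1.4% | 0.9% | 0.5% | 90.9% |
| 0.10 | 3.0% | 1.9% | 1.0% | 91.4% |
| 0.25 | 9.4% | 5.7% | 3.0% | 93.3% |

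Put per covariate, three mutually independent covariates each correlated r with HbA1c give R² = 3r². At ρ = 0.5 the SE falls by 0.5% (r = 0.1), 2.3% (r = 0.2) or 6.4% (r = 0.3; 0.153 to 0.143).

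**4. Why baseline matters.** If the primary model ignored baseline HbA1c, the gain would be 1 − √(1 − R²), or 5.1% at R² = 0.10. With baseline in the model at ρ = 0.5 it is 1.9%.

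**5. Limits.** These figures ignore the clinic effect and assume complete data and the same covariate association at each visit. Selection at entry can disturb the last assumption, because HbA1c must be at least 0.5% above a target of 7% or 8%, and history of severe hypoglycaemia sets the target. One set of simulated trials with 216 evaluable participants and entry floors of 7.5% and 8.5% gave SE ratios of 0.982 to 0.999, a fall of 0.1 to 1.8%. Another set with entry floors gave gains similar to the formula. Neither showed a loss.

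**The case against.** The strongest reply is that nothing here is an error. The order of the analyses is pre-specified and Table 3 labels both. Leaving out a predictive covariate in a randomised trial biases neither the estimate nor the type I error, and the sample size does not rely on adjustment. All of that stands.

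It also stands that the primary model is not a bare comparison. It conditions on baseline HbA1c and clinic. A reader might infer that any chance imbalance in a predictor passes in full into the primary estimate. It does not: with equal association r at each visit, conditioning on baseline leaves r(1 − ρ), so at ρ = 0.5 half is already removed.

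A reader might also take the 6.4% as the expected loss and convert it to 14% more participants (1/0.936² = 1.14). The documents do not support that as a headline. It needs three independent covariates each correlated 0.3 with HbA1c, and the plan gives no correlations.

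Finally, adjustment has a practical cost if it is done carelessly. Table 2 provides for missing baseline values, and a standard mixed model drops participants with a missing covariate, contrary to the plan's inclusion of all participants. A 2% gain in SE is cancelled by losing about 4% of participants (1 − 0.98² = 0.040). This is a reason to state how missing covariates are handled, not a reason to leave the covariates out.

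**Conclusion.** The point holds as a modest loss of efficiency with a mislabelled rationale. The primary analysis is valid and unbiased and meets its planned power. It would be wrong to infer from the word confounders that the unadjusted result is confounded, because allocation is randomised.

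Under the assumptions above, the primary standard error is larger than it need be by roughly 0 to 3% for joint R² up to about 0.10, and by about 6% (at ρ = 0.5) only if all three covariates are strong. The most favourable corner examined, R² = 0.25 with ρ = 0.3, gives 9.4%. A narrower interval is expected, but it is not guaranteed in a single data set. The case for change rests less on the size of the gain than on its low cost: the adjusted model is already written, targets the same quantity, and is expected to match or improve on the precision of the present one.

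**What to change.** - In Primary and secondary outcomes, name the constrained longitudinal model with age, IRSD and history of severe hypoglycaemia as fixed effects as the primary analysis of 12-month HbA1c. Keep the model without them as supportive.
- Describe the three variables as prognostic baseline covariates.
- State that participants with a missing baseline covariate are retained, for example by simple or mean imputation, so that all participants stay in the analysis.
- Mark the adjusted column of Table 3 as primary.

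No new data or participants are needed. Age and history of severe hypoglycaemia bear on eligibility or the target (Inclusion criteria), and IRSD comes from postcode (Table 2 notes), so few values should be missing. The article says it was written before data collection was complete, so the change can be made before outcome analysis. If the published protocol, which is not shown, names the primary model, the change should be recorded against it too.

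The small downside is that the headline result becomes the covariate-adjusted one. The subgroup analyses and the pattern-mixture sensitivity analysis, which are built on the primary model, follow it.
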